### Missing data and dropouts

Patients who discontinue or withdraw from the trial for any reason during the trial can be treated with disease-specific therapies and will not adversely affect their subsequent treatment, including supplemental SLNB, ALND, radiotherapy and other therapies as appropriate, after obtaining informed consent. For missing data, we will not perform any imputation. Instead, we will use the last observation carried forward method, which helps to maintain the integrity of the ITT analysis.

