### Endpoints

#### Primary endpoint

The primary endpoint of this trial is 3 year invasive disease-free survival (iDFS), defined as the time from surgery to local recurrence, regional recurrence, distant metastasis, infiltration of the contralateral breast cancer or death from any cause, whichever occurs first.

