### Sample size calculation

In this study, we used PASS software (version 2021) to perform a sample size calculation for a one-proportion non-inferiority test. The sample size was based on the primary endpoint of iDFS. According to the literature exploration and previous research results, it is expected that the 3 year iDFS in patients undergoing SLNB is about 90%. We set the non-inferiority margin at 5%, with a power of 80%, a significance level (α) of 0.05 and a 95% CI. Considering a 10% dropout rate, PASS software calculated the required sample size to be 311 patients.

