### Statistical analysis

The primary analysis will use an intention-to-treat (ITT) analysis. For categorical variables, the χ2 test or Fisher’ s exact test will be used, and the data will be presented as totals, percentiles and frequencies. For continuous variables, descriptive statistics will be analysed using mean, SD or median and IQR. Independent samples t-tests will be used for normally distributed continuous variables, and nonparametric tests will be used for skewed data to analyse the results. Kaplan–Meier curves and log-rank tests will be used to determine the statistical significance of variables in the survival outcome categories (iDFS) and survival curves will be plotted. The prognostic significance of variables will be assessed using univariate and multivariate COX risk regression analyses. HR and 95% CI will be calculated. For each statistical analysis, a p value <0.05 will be considered statistically significant.

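### The missing-data rule forbids imputation and then adopts last observation carried forward with no endpoint exempted; if it reaches 3-year iDFS, it favours non-inferiority

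*Protocol article*

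**What the plan says.** All places are in the protocol article.

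- **Missing data and dropouts** says "For missing data, we will not perform any imputation. Instead, we will use the last observation carried forward method", and justifies this as protecting the ITT analysis. It names no endpoint and exempts none.
- **Statistical analysis** says "The primary analysis will use an intention-to-treat (ITT) analysis". For iDFS it says "Kaplan–Meier curves and log-rank tests will be used to determine the statistical significance of variables in the survival outcome categories (iDFS"), followed by Cox regression.
- **Primary endpoint** says "The primary endpoint of this trial is 3 year invasive disease-free survival (iDFS), defined as the time from surgery to local recurrence" or another listed event, so iDFS is a time to event.
- **Sample size calculation** used PASS to "perform a sample size calculation for a one-proportion non-inferiority test", with 90% expected, a 5-point margin, 80% power and α of 0.05. It ends "Considering a 10% dropout rate", giving 311 patients. It does not say whether α is one-sided or two-sided.
- **Data collection and management** keeps and uses data gathered before consent was withdrawn, for up to 3 years afterwards.
- **Consent or assent** leaves patients who withdraw completely out of the final analysis.

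**The concern.** Carrying the last value forward replaces a missing value with a single assumed one, which is imputation. An analyst who obeys either sentence breaks the other. An unseen analysis plan cannot resolve this, because any choice it makes contradicts a rule already published.

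For the serial measures (arm volume and bioimpedance for BCRL, FACT-B, Quick DASH), a value from the first weeks or months would stand as the 3-year value. A patient lost while free of BCRL would count as free at 3 years. A frozen questionnaire score would be analysed as if observed, with intervals that are too narrow. The case for better quality of life and less arm morbidity rests on these outcomes.

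For iDFS the stake is the primary claim. The rule is justified by the ITT analysis, which is the primary analysis, and a one-proportion test needs a 3-year status for each patient. If LOCF supplies it, someone last seen event-free at 6 months becomes event-free at 36 months. In a single-arm comparison with a fixed limit, no control arm offsets that error, and it points towards declaring omission of SLNB safe.

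**Working it through.** **1. Reproduce the planned size.** Inputs from Sample size calculation: p1 = 0.90, limit p0 = 0.90 − 0.05 = 0.85, power 80%, α 0.05, dropout 10%.

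n = [z(1−α)·√(p0(1−p0)) + z(power)·√(p1(1−p1))]² / (p1 − p0)²

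- One-sided 0.05: [1.645·√0.1275 + 0.842·√0.09]² / 0.0025 = 282.1, so 283. With dropout: 283 × 1.1 = 311.3 (312), or 283/0.9 = 314.4 (315).
- Exact binomial, one-sided 0.05: smallest n is 281, giving 310 (× 1.1) or 313 (/0.9).
- The stated 311 lies within this range of 310 to 315.
- One-sided 0.025 with the formula above gives 363 (404 after dividing by 0.9), which does not match. However, a Wald formula using only the p1 variance at one-sided 0.025 also gives 283. So 311 does not settle the sidedness, and both levels are shown below.

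**2. Test cut-offs at N = 311, p0 = 0.85 (exact binomial).**

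- One-sided 5%: at least 275 event-free, actual size 4.99%.
- One-sided 2.5%: at least 277 event-free, actual size 2.34%.

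**3. What LOCF does to 3-year status.** Assumptions: exponential iDFS with S = 0.85 at 3 years; a fraction d drops out evenly over the 3 years, unrelated to prognosis; a dropout counts as event-free unless the event came first. Let H = −ln S = 0.1625.

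Apparent event-free proportion = S + d·[1 − S(1 + H)]/H

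[1 − 0.85 × 1.1625]/0.1625 = 0.0730

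At d = 0.10: 0.85 + 0.10 × 0.0730 = 0.8573. That is 0.0073 × 311 ≈ 2.3 patients wrongly counted as event-free.

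**4. Probability of declaring non-inferiority when true iDFS is 85%.**

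| Handling of dropout | Apparent iDFS | One-sided 5% | One-sided 2.5% |
|---|---|---|---|
| No dropout, or non-informative dropout censored by Kaplan–Meier | 85.0% | 5.0% | 2.3% |
| LOCF, 5% dropout, even (assumed rate) | 85.4% | 7.1% | 3.5% |
| LOCF, 10% dropout, even (planned rate) | 85.7% | 9.8% | 5.1% |
| LOCF, 10% dropout, all at the start (1 − 0.9 × 0.15) | 86.5% | 18.2% | 10.5% |
| LOCF, 20% dropout, even (assumed rate) | 86.5% | 17.7% | 10.1% |

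**5. Informative dropout (assumed; the article gives no figure).** Take 10% dropout, overall true iDFS still 85%, one-sided 5%. The Kaplan–Meier column applies the same binomial rule to its limiting value, so it is approximate.

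| Event hazard in dropouts | LOCF: false non-inferiority | Kaplan–Meier: apparent iDFS | Kaplan–Meier: false non-inferiority |
|---|---|---|---|
| 2 times | 14.8% | 85.6% | about 8.5% |
| 3 times | 19.3% | 86.0% | about 12.0% |

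Here LOCF adds about 6 to 7 percentage points to the error of Kaplan–Meier, which is no longer unbiased.

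**6. Withdrawals, set side by side.** ITT keeps everyone; the missing-data section carries the last value forward; Data collection and management keeps and uses earlier data; Consent or assent drops complete withdrawals. As written, these give the same patient different treatment.

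No figure is given for BCRL, FACT-B or Quick DASH, because the article states no expected values for them.

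**The case against.** A reader might infer that LOCF governs the primary endpoint, that every dropout therefore counts as event-free at 3 years, and that the trial is certainly biased towards non-inferiority. The documents do not support this.

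- No section applies LOCF to iDFS. The endpoint is a time to event, and the only methods named for it (Kaplan–Meier, log-rank, Cox) censor dropouts. LOCF is a repeated-measures device and fits the arm and questionnaire data better.
- The one-proportion test appears only as the basis of the sample size, not as the stated primary analysis.
- Complete withdrawals are to be excluded, not carried forward.
- At the planned 10% with non-informative, evenly spread dropout, the shift is 0.7 points against a 5-point margin. The 20% rate and the doubled or tripled hazards have no source in the article, and informative dropout would bias Kaplan–Meier too.

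These points stand, and they make the iDFS bias conditional. They do not remove it. The rule exempts no endpoint and is tied to ITT. Kaplan–Meier and log-rank are assigned to the significance of variables, and the article never says which estimate is compared with 85%.

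It can also be said that complete withdrawal may be a narrower category than withdrawal of consent, which would ease the conflict over retained data. The article does not define the difference. Finally, the choice of model for the secondary endpoints is normally left to an analysis plan. That is fair for details, but not for a published rule that imposes LOCF on them.

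**Conclusion.** The contradiction is certain on the text, and LOCF as written reaches the BCRL, FACT-B and Quick DASH data, where it replaces missing 3-year values with earlier ones.

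The effect on iDFS is conditional on LOCF-filled status being used in a one-proportion test. In that case, with the planned 10% dropout and the assumptions in step 3, false non-inferiority roughly doubles at either significance level. Earlier or heavier dropout, or dropout linked to prognosis, would enlarge this, but those are assumptions and not features of the plan. With Kaplan–Meier censoring and non-informative dropout, this bias does not arise.

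The handling of withdrawals is inconsistent across four sections, and deleting LOCF alone would not resolve it. Because one plausible reading distorts the primary claim and the repair is nearly free, the text should be corrected before any analysis.

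**What to change.** 1. Delete both sentences: the ban on imputation and the adoption of LOCF.
2. State that the Kaplan–Meier 3-year iDFS, with patients censored at their last disease assessment, is the estimate whose confidence limit is compared with 85%, and state the sidedness. Add a sensitivity analysis that raises the event hazard after dropout until non-inferiority is lost.
3. Analyse FACT-B and Quick DASH on all observed visits with a mixed model for repeated measures. Analyse BCRL as time to first occurrence, censored at the last arm assessment.
4. Reconcile Data collection and management and Consent or assent with ITT by keeping data collected before withdrawal in the analysis. Define complete withdrawal if it is meant to differ from withdrawal of consent.

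The cost is about one paragraph of protocol or analysis-plan wording and one extra analysis. No new data are needed.

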### Data monitoring

An independent DSMB will be established for this study and will be reviewed every 6 months. The Data Supervision Committee will be responsible for the supervision and management of the research process and the authenticity of the data. The Safety Monitoring Board will be responsible for monitoring and analysing the adverse events (AEs) of the trial and guiding the management of AEs in accordance with the operational procedures and clinical principles. Any serious adverse events (SAEs) that occur during the course of this clinical trial will follow the National Cancer Institute’s Criteria for Common Toxic Reactions (NCI/CTCAE v5.0). The investigator will report in writing all SAEs, suspected and unexpected SAEs, and unexpected events that occur during the trial to the sponsor and the ethics committee within 24 hours of becoming aware of them. This will ensure that patients are treated promptly and documented in detail. Interim analyses will be performed by a statistician and reported to the DSMB, which will have access to all data and will discuss the results of interim analyses with the principal investigator and report to the ethics committee, which will ultimately decide whether the study should proceed.

### Ethics and dissemination

The study will be conducted in strict accordance with the tenets of the Declaration of Helsinki, and all patient data will be processed anonymously. The protocol was approved by the Ethics Committee of the First Affiliated Hospital of Nanjing Medical University on 16 May 2023 (Len review number: 2023 SR-193). Any amendments to the approved clinical trial protocol, informed consent and other study materials will be reviewed by the Ethics Committee of the First Affiliated Hospital of Nanjing Medical University and implemented after approval. The results of this study will be disseminated through academic conferences and peer-reviewed journals.

### Trial status

The protocol version number and date were V3.0 and 21 May 2023. The study was conceived and designed in 2022. The first patient was enrolled on 28 June 2023, and enrolment is expected to be completed in June 2026. At the time of manuscript submission, the study was in the process of enrolling patients.

### Consent or assent

Before any surgical procedures, researchers will provide a detailed explanation of the potential benefits and risks associated with the omission of SLNB to eligible and consenting participants. A dedicated period will be reserved to address all questions raised by the participants. Following this, the investigators will request that the participants sign an informed consent form. Participants have the right to withdraw from the study at any time and for any reason, without prejudice. Should a participant choose to withdraw completely, their data will not be included in the final data analysis.

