**Methods and analysis:**

The OMSLNB trial is a prospective, single-arm, non-inferiority, phase II, open-label study design involving female breast cancer patients with a tumor of ≤3 cm in diameter, who are considered axillary lymph-node-negative based on two or more radiological examinations, including axillary lymph node ultrasonography. Eligible patients will avoid axillary surgery but will undergo breast surgery, which is not limited to breast-conserving surgery. The trial begins in 2023 and is scheduled to end in 2027. The primary endpoint is 3 year invasive disease-free survival (iDFS). The secondary endpoints include the incidence of breast cancer-related lymphoedema, patient-reported outcomes, locoregional recurrence, local recurrence and regional recurrence. It is expected that the 3 year iDFS in patients undergoing SLNB is about 90%, combined with a non-inferiority cut-off of 5%, 80% power, 95% CIs, 0.05 test level, and 10% loss to follow-up rate, the planned enrollment is 311 patients. All enrolled patients will be included in the intention-to-treat analysis.

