### Clinical intervention and follow-up

After obtaining informed consent, axillary surgery will be omitted for eligible patients, and BCS or mastectomy (allowing breast reconstruction) will be voluntarily selected by the patient under the premise of ensuring therapeutic efficacy. Patients receiving BCS must undergo whole breast irradiation (WBI) after surgery, and postoperative adjuvant therapy and other treatments will be performed according to clinical guidelines.

Multiple timepoints will be established for dynamic follow-up at baseline and up to 3 years postoperatively, with a comprehensive and objective assessment of breast cancer-related lymphoedema (BCRL) using multi-segmental arm circumference measurements and bioelectrical impedance analysis at baseline, 1 week, 1, 3, 6, 12, 18, 24, and 36 months postoperatively, respectively. Patients will be administered a QoL questionnaire using the validated FACT-B (Version 4.0) and Quick DASH at the same time point.^30 31^ BCRL incidence and QoL will be subjectively assessed by patients using patient-reported outcomes (PROs).

Patients who discontinue or withdraw from the trial for any reason during the trial can be treated with disease-specific therapies, including supplemental SLNB, ALND, radiotherapy and other therapies as appropriate, after obtaining informed consent.

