### Data collection and management

This study uses an electronic case report form to manage and record the study data, and a password-protected access system will be set up to maintain participant confidentiality. The principal investigator has full responsibility of entire projects of this trial. The researchers needed to ensure that the data entry and correction were timely, complete, accurate and truthful. To ensure the accuracy of the data, double-entry and proofreading will be done independently by two data administrators. The clinical supervisor will perform data checking after the end of the study. The researcher will reply and follow-up on corrections promptly when the data are found to be incomplete inconsistent are challenged. If a subject withdraws their informed consent during participation in a clinical trial, no data will be collected after withdrawal. Study-related data collected before withdrawal will be retained and used for up to 3 years after withdrawal. At the end of the study, the principal investigator will submit a final report for review and written approval by the ethics committee.

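### Leaving complete withdrawals out of the final analysis contradicts the all-enrolled ITT analysis, is not reconciled with the 3-year data-retention rule, and can bias 3-year iDFS in either direction

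*Protocol article*

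**What the plan says.** The protocol article deals with patients who leave in five places.

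- **Abstract, Methods and analysis:** "All enrolled patients will be included in the intention-to-treat analysis".
- **Statistical analysis:** "The primary analysis will use an intention-to-treat (ITT) analysis".
- **Data collection and management:** after consent is withdrawn, "no data will be collected after withdrawal". On what was recorded before: "Study-related data collected before withdrawal will be retained and used for up to 3 years after withdrawal".
- **Missing data and dropouts:** there is no imputation, but "we will use the last observation carried forward method, which helps to maintain the integrity of the ITT analysis".
- **Consent or assent:** "Should a participant choose to withdraw completely, their data will not be included in the final data analysis".

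The article does not define complete withdrawal or separate it from the withdrawal of consent covered under data management. It does not say how often, when or why patients are expected to withdraw, beyond a 10% dropout allowance in the sample size.

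**The concern.** An ITT analysis of all enrolled patients and an analysis without complete withdrawals are different analysis sets. The first is fixed at enrolment. The second depends on something that happens later and may be related to outcome. The choice matters more than usual here: the trial has one arm and is judged against a fixed limit (90% expected, less a 5-point margin), so no control group would share the distortion. It is also open-label, and patients who leave may go on to axillary surgery or radiotherapy, so a link between leaving and prognosis is plausible.

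The appeal to last observation carried forward does not help, because a deleted patient has no observation to carry. The 3-year limit adds a second route by which observed follow-up and events could be lost before the final analysis.

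**Working it through.** **1. The rules applied to one patient.** Take a patient who has a recurrence at 12 months and withdraws completely at 14 months.

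| Section | Result for this patient |
|---|---|
| Abstract; Statistical analysis | In the ITT analysis |
| Data collection and management | Recurrence usable, but only until 3 years after withdrawal |
| Consent or assent | Not in the final analysis |

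The first and third rows cannot both hold. The second and third agree only if withdrawing completely means revoking permission for data already collected. The article does not say so, and the first row would still be broken.

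**2. The 3-year limit.** The first patient was enrolled on 28 June 2023, enrolment is expected to finish in June 2026 (Trial status), and follow-up is 3 years after surgery (Trial design and setting). The last patient therefore completes in about June 2026 + 3 years = June 2029. At an analysis then, data from anyone who withdrew before June 2026 would be past the limit. The abstract schedules the end for 2027; at the end of that year, withdrawals before the end of 2024 would be past it.

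**3. The planned sample size.** Inputs from Sample size calculation: p1 = 0.90, margin 0.05 so p0 = 0.85, power 0.80, α = 0.05 (sidedness not stated), 10% dropout, N = 311. With one-sided α = 0.05:

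n = [1.645·√(0.85·0.15) + 0.842·√(0.90·0.10)]² / 0.05² = 282.1, so 283.

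The exact binomial test first reaches 80% power at n = 281. Allowing for dropout, 281/0.9 gives 313 and 281 × 1.1 gives 310; from 283 the figures are 315 and 312. All are close to 311. The steps below use N = 311 and the exact one-sided test against 0.85.

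**4. Deleting patients who had an event.** With X ~ Binomial(n, 0.85) event-free patients, p = P(X ≥ n − events).

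| Events / n | Observed iDFS | One-sided p | At 0.05 | At 0.025 |
|---|---|---|---|---|
| 37/311 | 0.881 | 0.070 | fails | fails |
| 35/309 (two events deleted) | 0.887 | 0.038 | passes | fails |
| 35/311 | 0.887 | 0.035 | passes | fails |
| 34/310 (one event deleted) | 0.890 | 0.0247 | passes | passes |

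Near the boundary, deleting two patients changes the conclusion at 0.05 and deleting one changes it at 0.025.

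**5. Deleting patients who were event-free.** Assume constant hazards and withdrawal unrelated to prognosis. For true iDFS 0.85, the event hazard is λ = −ln(0.85)/3 = 0.0542 per year. For 10% withdrawal, θ = −ln(0.90)/3 = 0.0351.

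- Event-free to 3 years without withdrawing: 0.85 × 0.90 = 0.765.
- Event before withdrawal: λ/(λ+θ) × (1 − 0.765) = 0.1426.
- Withdrew event-free: 1 − 0.765 − 0.1426 = 0.0924.

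Deleting the last group leaves 0.765/(0.765 + 0.1426) = 0.843. For true iDFS 0.90 the same steps give 0.81/(0.81 + 0.095) = 0.895. Censoring these patients in a Kaplan–Meier estimate would leave 0.850 and 0.900 unbiased.

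**6. Deletion related to prognosis.** Suppose 10% are deleted (280 left), true iDFS in all enrolled is 0.85, and deleted patients have k times the hazard of the rest. Solve 0.9·S + 0.1·S^k = 0.85 for S in the retained patients. The test passes with 249 or more of 280 event-free, which has probability 3.6% at S = 0.85.

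| Who is deleted | k = 2: retained iDFS, P(pass) | k = 3: retained iDFS, P(pass) |
|---|---|---|
| All withdrawers, recorded events included | 86.2%, 10.5% | 87.1%, 20.7% |
| Only those event-free at withdrawal (time uniform over 36 months) | 84.9%, 3.3% | 85.4%, 5.2% |

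The inflation depends mainly on whether recorded events are erased.

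**The case against.** The tempting stronger reading is that deletion favours non-inferiority. The documents do not support that as a general statement. They give no reasons, timing or event rates for withdrawal. Step 5 moves the estimate downwards, and the larger figures in step 6 need three assumptions together: that the whole 10% dropout allowance is complete withdrawal, that these patients have two to three times the hazard, and that recorded recurrences are erased. The article describes the 10% as dropout or loss to follow-up, which is wider than complete withdrawal.

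A reader might also infer that patients given supplemental axillary treatment leave the data. The text does not say so. Clinical intervention and follow-up says only that those who discontinue or withdraw "can be treated with disease-specific therapies, including supplemental SLNB, ALND, radiotherapy and other therapies as appropriate"; it does not remove them from follow-up or from the analysis.

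It can fairly be said, too, that the data-management and consent sections are partly compatible if complete withdrawal means revoking permission to use existing data. The full protocol and consent form, not shown here, may define it so. That would soften the conflict between those two sections. It would not restore an analysis of all enrolled patients.

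Finally, censoring is not a full cure. In the model of step 6 with withdrawal uniform over 36 months, censoring at withdrawal gives a Kaplan–Meier limit of about 85.6% at twice the hazard and 86.0% at three times, against a true 85%. Some bias from informative censoring remains, and the fix has to allow for it.

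**Conclusion.** The contradiction is in the printed text and stands: excluding complete withdrawals is incompatible with an ITT analysis of all enrolled patients. It is also unreconciled with the rule that earlier data are retained and used, and that rule's 3-year limit can expire before the final analysis for early withdrawals.

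The effect on 3-year iDFS can go either way. It is towards non-inferiority if withdrawal follows recurrence or higher risk, where one or two deleted events can reverse a result near the boundary. It is against non-inferiority if the deleted patients were event-free, by about 0.7 points at a true 85% with 10% non-informative withdrawal (0.850 to 0.843). Both figures are illustrations. They rest on assumed numbers and reasons for withdrawal and, in step 5, on constant hazards. The planned 311 is unaffected. The rule decides who enters the primary analysis and should be settled before outcomes are known.

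**What to change.** Use one rule in the abstract, Data collection and management, Missing data and dropouts, and Consent or assent:

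- Keep all enrolled patients in the primary analysis. Use data collected up to withdrawal of consent, count iDFS events that occurred before it, and otherwise censor at the last disease assessment.
- Retain these data until the final analysis is complete, in place of the limit of 3 years after withdrawal.
- Distinguish stopping the assigned management from withdrawing consent. In the former, iDFS follow-up continues unless the patient refuses it.
- Exclude data only where a patient withdraws permission to use data already collected. Report the number and timing of such exclusions.
- Add a sensitivity analysis that counts withdrawals as events, because censoring may itself be informative. Present it as a bound: the exact test at 0.05 allows 36 events in 311, so if 31 patients (10%) withdrew and were counted, only 36 − 31 = 5 other events would be allowed.

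The cost is revised protocol and consent wording with ethics review. No new procedure and no change in sample size is needed. Patients who have already consented keep whatever their signed form promises.
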